# A randomized controlled trial to reduce sedentary time in rheumatoid arthritis: protocol and rationale of the Take a STAND for Health study

**DOI:** 10.1186/s13063-020-4104-y

**Published:** 2020-02-12

**Keywords:** Sitting, Light-intensity physical activity, Rheumatic arthritis

## Abstract

**Background:**

Patients with rheumatoid arthritis spend most of their daily hours in sedentary behavior (sitting), a predisposing factor to poor health-related outcomes and all-cause mortality. Interventions focused on reducing sedentary time could be of novel therapeutic relevance. However, studies addressing this topic remain scarce. We aim to investigate the feasibility and efficacy of a newly developed intervention focused on reducing sedentary time, and potential clinical, physiological, metabolic and molecular effects in rheumatoid arthritis.

**Methods:**

The Take a STAND for Health study is a 4-month, parallel-group, randomized controlled trial, in which postmenopausal patients with rheumatoid arthritis will set individually tailored, progressive goals to replace their sedentary time with standing and light-intensity activities. Patients will be recruited from the Clinical Hospital (School of Medicine, University of Sao Paulo) and will be assessed at baseline and after a 4-month follow up. Outcomes will include objectively measured sedentary behavior (primary outcome) and physical activity levels, clinical parameters, anthropometric parameters and body composition; aerobic fitness, muscle function, blood pressure, cardiovascular autonomic function, vascular function and structure, health-related quality of life, and food intake. Blood and muscle samples will be collected for assessing potential mechanisms, through targeted and non-targeted approaches.

**Discussion:**

Findings will be of scientific and clinical relevance with the potential to inform new prescriptions focused on reducing sedentary behavior, a modifiable risk factor that thus far has been overlooked in patients with rheumatoid arthritis.

**Trial registration:**

ClinicalTrials.gov, NCT03186924. Registered on 14 June 2017.

## Introduction

Rheumatoid arthritis is an autoimmune disease characterized by chronic inflammation, joint damage, pain, fatigue, and physical disability [1]. Patients with rheumatoid arthritis have a greater risk of cardiovascular disease and premature mortality, which are partially explained by the complex interplay between chronic inflammation, adverse effects of drugs, associated comorbidities (e.g., dyslipidemias, insulin resistance, hypertension), and lifestyle [2–4]. Physical inactivity and sedentary behavior are modifiable risk factors that can aggravate disease symptoms and contribute to poor health outcomes [5].

The role of physical activity in the management of rheumatoid arthritis has dramatically shifted. In the 1970’s, bed rest and immobilization were recommended [6]. Now, it is well-known that exercise training improves disease symptoms, cardiometabolic risk factors, and physical fitness, which together may confer protection against premature mortality [7–9]. However, participation in higher-intensity physical activity may not be suitable for patients with rheumatoid arthritis, especially those with disabilities and active disease, conditions that may restrict moderate-to-vigorous physical activity. Light-intensity physical activity has been recently associated with lower cardiovascular risk, disability, and disease activity in rheumatoid arthritis [10]. Thus, interventions focused on replacing sedentary time with light-intensity physical activity could be of high clinical relevance.

Sedentary behavior (sitting) is strongly associated with poor health outcomes (e.g., cardiovascular disease, type 2 diabetes mellitus, some cancers) and all-cause mortality [11, 12]. Controlled laboratory studies have shown that active breaks in sedentary time (e.g., 2-min light-walking breaks every 20 min) for 5–8 h can improve cardiometabolic risk factors (e.g., reduced postprandial glucose and insulin) in general and clinical populations [13, 14]. Intervention studies focused on reducing sedentary time have also shown improvements in insulin sensitivity, lipid profile, body composition, and blood pressure in the general population and in the obese [15–17]. However, the impact of reducing sedentary time in rheumatoid arthritis remains underexplored.

Patients with rheumatoid arthritis spend 10.3 h/day on average in sedentary behavior [10, 18–21], which exceeds that in the general population (~ 7.5 h) [22], but is comparable to that in other clinical conditions (~ 9.4 h; pooled data for cardiovascular diseases [23], type 2 diabetes mellitus [24, 25]), and obesity [26, 27]). In these latter conditions, sedentary behavior is consistently related to morbidity and mortality [28–30]. Despite the paucity of evidence, it is plausible to assume that this might also hold true for patients with rheumatoid arthritis, since they commonly have cardiometabolic risk factors that can be aggravated by sedentary behavior [2–4]. To our knowledge, only a single study has addressed this topic, showing that an intervention involving general motivational counseling and text-message reminders resulted in reduced sedentary time (1.6 h/day), pain, and fatigue and improved quality of life in a Scandinavian cohort of patients with rheumatoid arthritis [31]. The cross-cultural validation of this finding in a Latin-American cohort with a lower socioeconomic status is necessary. In addition, exploring the putative mechanisms underlying the effects of reducing sedentary time requires novel studies. We aim to investigate the effects of a newly developed intervention focused on reducing sedentary time and its clinical, physiological, metabolic, and molecular effects in patients with rheumatoid arthritis.

## Materials and methods

### Objectives and hypotheses

We will test the feasibility and efficacy of a newly developed personalized intervention focused on replacing sedentary time with light-intensity physical activity in patients with rheumatoid arthritis. A multitude of techniques will be applied to evaluate the effects of the intervention on several outcomes, including sedentary time (primary outcome), physical activity levels, clinical parameters, cardiometabolic risk factors, and health-related quality of life. In addition, molecular analyses will be conducted in skeletal muscle and blood samples to gather knowledge on the potential underlying mechanisms by using targeted and non-targeted omic approaches. Finally, responders and non-responders (based on the reduction of sedentary time) will be compared to test the efficacy of reducing sedentary behavior on health-related outcomes in rheumatoid arthritis.

Our two main hypotheses are that (1) the intervention will be effective in reducing sedentary time, and (2) reducing sedentary time will improve clinical parameters, cardiometabolic risk factors, and health-related quality of life.

### Experimental design

We will conduct a 4-month, parallel-group, randomized controlled trial, in which patients will be assessed at baseline (PRE) and after 4 months (POST) for sedentary behavior (primary outcome) and physical activity levels; clinical parameters; anthropometric parameters and body composition; aerobic fitness; muscle function; blood pressure; cardiovascular autonomic function; vascular function and structure; health-related quality of life; blood samples and oral glucose tolerance test; immune function; muscle biopsy; and food intake. Sedentary behavior and physical activity levels will be also evaluated at the second month to check adherence to the intervention.

After baseline assessments, patients will be randomly allocated to either a control or intervention group using a simple randomization (1:1 ratio) procedure, by computer-generated random numbers in SAS 9.3 (SAS Institute Inc., Cary, NC, USA) for Windows. An external researcher will generate the allocation sequence and be contacted after patients’ enrollment. All assessors will be blinded to patients’ allocation and will be responsible for patients’ recruitment and enrollment. However, a trained researcher who will not be blinded to patients’ allocation will be responsible for assigning patients, and for applying and monitoring the Take a STAND for Health intervention. The control group will receive standard care, including general advice on healthy lifestyle. The intervention group will receive standard care supplemented with a specific personalized intervention aimed at reducing sedentary time (called Take a STAND for Health), which will not require alteration to usual care pathways (including use of any medication). In brief, this intervention comprises individually tailored progressive goals aimed at reducing sedentary time, which will be selected with the active participation of the patient. A trained researcher will assess adherence to the goals via phone calls and personal interviews throughout the follow up.

The current study is registered in an international database of clinical research studies (clinicaltrials.gov, NCT03186924). This manuscript is described according to the Standard Protocol Items: Recommendations for Interventional Trials (SPIRIT) checklist (Fig. 1, Additional file 1) and the findings from this study will be reported according to the recommendations of the Consolidated Standards of Reporting Trials (CONSORT) guidelines (Fig. 2).

**Fig. 1 Fig1:**
[figure not shown]
Overall schedule of enrollment, intervention, and assessments following the Standard Protocol Items: Recommendations for Interventional Trials (SPIRIT) checklist

**Fig. 2 Fig2:**
[figure not shown]
Consolidated Standards of Reporting Trials (CONSORT) flow diagram

### Patient recruitment and selection

Patient recruitment and selection will take place at the Clinical Hospital (School of Medicine, University of Sao Paulo). Postmenopausal patients diagnosed with rheumatoid arthritis (*N* = 30) [32] will be recruited directly from the Rheumatoid Arthritis Outpatient Clinic of the Rheumatology Division. The exclusion criteria include (1) participation in structured exercise training programs within the last 12 months; (2) unstable drug therapy in the last 3 months prior to and during the study; (3) Health Assessment Questionnaire score > 2.0 (i.e., severe physical impairment).

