#### Clinical assessment

Disease activity will be assessed by the Disease Activity Score in 28 joints [37], which is based on the number of tender and swollen joints, C-reactive protein or erythrocyte sedimentation rate, and the patient’s general health status. Higher scores represent more severe disease activity. The Health Assessment Questionnaire [38], which evaluates physical functioning in eight domains of daily life, will also be used; higher scores represent greater disability. Disease duration, current dose of prednisone, current use of biological agents (e.g., anti-TNF, anti-IL6, anti-IL1, B cell depleting-agents, and T cell activation-inhibiters), non-biological disease-modifying anti-rheumatic drugs (e.g., methotrexate, leflunomide, and hydroxychloroquine), and other medications will be obtained by reviewing medical records and interviewing patients. Pain will be assessed using a visual analogic scale [39], in which patients grade their pain using a 10-point scale; 0 means no pain and 10 means severe or unbearable pain. Fatigue will be assessed by the Fatigue Severity Scale [40] in which lower scores indicate lower fatigue.

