### Statistical analysis

Data normality will be tested using the Kolmogorov-Smirnov or the Shapiro-Wilk *W* test. Parametric data will be presented as mean ± 95% CI. Non-parametric data will be log-transformed and presented as back-transformed mean ± 95% CI. The ES (Cohen’s *d*) will be calculated and interpreted as small (0.2–0.4), medium (0.5–0.7), or large (≥ 0.8).

Generalized linear mixed model analyses will be performed for each dependent variable, with group and time as fixed factors and patients as a random factor; the models will be adjusted by age, BMI, disease activity, and if different between groups, baseline values of the outcome variable. In the case of significant *F* values, a post-hoc test with Tukey’s adjustment for multiple comparisons will be performed. Analyses will be conducted according to the intention-to-treat principle, in which missing values will be handled by the generalized linear mixed model by using maximum likelihood to estimate the parameters of the model. To test the influence of reducing sedentary time on health-related outcomes, patients will be allocated into “responder” and “non-responder” sub-groups (according to changes in sedentary time); thereafter, the dependent variables will be compared between them.

Data analysis will be performed using the SAS 9.3 (SAS Institute Inc., Cary, NC, USA) for Windows. The level of significance will be set at *p* ≤ 0.050.

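### The exclusion for unstable drug therapy extends past randomization, is in tension with the intention-to-treat analysis, and the article does not say what follows when a randomized patient's drugs change

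*Protocol article*

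**What the plan says.** Under Patient recruitment and selection the article gives three exclusion criteria. The list opens with "The exclusion criteria include (1) participation in structured exercise training programs within the last 12 months", and its second item is "unstable drug therapy in the last 3 months prior to and during the study". The wording therefore stands as an eligibility exclusion, not as an instruction on concomitant treatment.

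Under Experimental design, allocation comes after baseline: "After baseline assessments, patients will be randomly allocated to either a control or intervention group using a simple randomization (1:1 ratio) procedure". Follow-up then runs for 4 months. The same section says that the intervention requires no change to usual care, medication included. It does not say what happens if medication does change.

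Under Statistical analysis: "Analyses will be conducted according to the intention-to-treat principle", and "missing values will be handled by the generalized linear mixed model by using maximum likelihood to estimate the parameters of the model".

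Under Clinical assessment: "Disease activity will be assessed by the Disease Activity Score in 28 joints". HAQ, pain and fatigue are measured as well, and prednisone dose, biological agents, other disease-modifying drugs and remaining medication are taken from records and interviews.

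**The concern.** An exclusion criterion can use only what is known before allocation. Stability of therapy during follow-up is not known then. In rheumatoid arthritis a change of drugs plausibly follows disease activity and pain, which are outcomes here. The second hypothesis under Objectives and hypotheses says that reducing sedentary time will improve clinical parameters. If that is true and the criterion is applied as written, the two arms would lose different patients at different rates, and the clinical comparison would no longer be between the groups as randomized.

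Two features of the design add to this. The intervention arm has five face-to-face sessions and weekly calls or messages, while controls receive standard care with general advice, so drug changes could come to light more often in one arm. The researcher who assigns patients and monitors the intervention is also unblinded, and the article does not define unstable therapy.

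**Working it through.** **Passages side by side**

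1. The criterion covers two periods: the 3 months before the study, and the study itself.
2. Randomization follows baseline. The first period can be checked before allocation; the 4 months of follow-up cannot.
3. Intention to treat analyses patients as randomized, whatever happens later.
4. Nothing in the article says whether a drug change after randomization leads to removal from the analysis, to the end of follow-up, or to nothing at all.

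The plan states no figure on this point, so there is none to reproduce.

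**Illustration of the possible bias**

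Every rate here is an assumption; the documents give none. Let the change in a clinical score have SD 1, with a true benefit of δ SD. A patient is removed when a flare index, correlated r with that change, exceeds a cut-off c. The cut-off is set so that a fraction q of controls is removed. With λ(x) = φ(x)/Φ(x):

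- fraction removed in the intervention arm = 1 − Φ(c + rδ)
- estimated benefit among those left = δ − r[λ(c) − λ(c + rδ)]

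Worked case: q = 10%, so c = 1.282; δ = 0.5; r = 1. Then λ(1.282) = 0.195 and λ(1.782) = 0.085. The estimate is 0.5 − (0.195 − 0.085) = 0.39. The fraction removed in the intervention arm is 1 − Φ(1.782) = 3.7%.

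Range over r from 1.0 to 0.4:

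| True benefit (SD) | Controls removed | Intervention removed | Estimate (SD) |
|---|---|---|---|
| 0 | 10% | 10% | 0 |
| 0.3 | 10% | 5.7% to 8.0% | 0.23 to 0.29 |
| 0.5 | 10% | 3.7% to 6.9% | 0.39 to 0.48 |
| 0.5 | 20% | 9.0% to 14.9% | 0.33 to 0.47 |

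A simulation of 1,000,000 patients per arm gives the same values to within rounding.

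**Direction is not fixed**

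Suppose instead that there is no true effect, but closer contact reveals more drug changes in the intervention arm: 20% removed there against 10% of controls, again assumed. The spurious benefit is r[λ(0.842) − λ(1.282)] = r(0.350 − 0.195). That is 0.06 SD at r = 0.4 and about 0.15 SD at r = 1, in favour of the intervention. The first scenario pulls the estimate towards no effect; this one pushes it away.

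**The case against.** The strongest reply is that the article never says these patients are removed. The criterion sits under a heading on recruitment and selection, and the only statement about who is analysed is intention to treat. The wording could mean that patients whose therapy is not expected to stay stable are not enrolled, or that a drug change ends participation. This stands, and it limits the point to a conflict on the literal reading.

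A reader might go further and infer that the two rules cannot both be followed. The documents do not support that. A patient withdrawn for a drug change could remain in the analysis set and contribute her observed baseline values, plus month-2 values for sedentary behavior and physical activity, under maximum likelihood. The reply only partly removes the concern. Clinical parameters are scheduled at baseline and 4 months only, so a patient withdrawn in between has no clinical value after baseline. If the drug change followed a flare after baseline, the observed clinical scores would not carry that information. Maximum likelihood also does nothing for a patient deleted from the analysis set.

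A reader might also infer that the trial would fall well short of its required 24 patients because of this criterion. That cannot be shown either. No rate of drug change is given, and the article does not say whether the dropout allowance of about 25% already includes such withdrawals. The shortfall of 30 × 0.75 = 22.5 against 24 exists without this issue, and the article plans at least 30 patients.

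Finally, the exposed outcomes are secondary, and under the first scenario above the error is conservative. Both are true, though the second scenario shows that the error need not be conservative.

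**Conclusion.** The point holds as an unreconciled tension. Part of an exclusion criterion can be judged only after allocation; read literally, it would exclude randomized patients for an event plausibly linked to disease activity, and the intention-to-treat statement is not squared with it. This is something the article states, not a detail left to a fuller document.

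The consequence is possible bias in DAS28, HAQ, pain, CRP/ESR and SF-36. It arises only if patients are in fact removed, or lose their follow-up measurements, because of drug changes. Its direction and size are unknown; the illustrative figures depend wholly on assumed rates and correlations. Sedentary time is less directly exposed. It is worth correcting because the correction costs almost nothing and protects the randomized comparison.

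**What to change.** Reconcile Patient recruitment and selection with Statistical analysis:

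- Limit the eligibility criterion to the 3 months before randomization.
- State that all randomized patients stay in follow-up and in the intention-to-treat analysis, whatever happens to their drug therapy afterwards.
- Report by arm the medication data already collected under Clinical assessment.
- Allow an analysis restricted to patients without a therapy change only as a labelled sensitivity analysis.

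This concerns eligibility and analysis only and proposes no rule on drug treatment. It takes a one-line change to the criterion and a sentence or two in the analysis section. The small downside is that drug changes will add some noise to the clinical outcomes, which the sensitivity analysis can help to gauge.

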#### Sample size

Sample size calculations were performed using G-Power® software, v. 3.1 (Universität Düsseldorf, Düsseldorf, Germany), based on the study by Lewis et al. that reported the effects of reducing sedentary behavior in an elderly population (i.e., a reduction of 52 min in total sitting time) [33]. According to the estimation, 24 patients (12 per arm) are required to achieve 95% power (α), with a significance level of 5% (β), and assuming an effect size of 0.58 for the primary outcome (i.e., sedentary time). Estimating a dropout rate of ~ 25%, at least 30 patients will be recruited. Considering that this sample size could be underpowered for some secondary outcomes, we will try to increase this estimated sample based on the feasibilities of our laboratory (including funding, capacity of research staff and facilities, and available patients), in line with contemporary recommendations [34, 35].

#### Ethical compliance

This trial has been approved by the local Ethical Committee (Commission for Analysis of Research Projects, CAPPesq; approval: 1.735.096). Patients will be required to sign an informed consent form before participation and all the procedures will be conducted in accordance with the Declaration of Helsinki revised in 2008. Patients will provide formal consent to share their data and samples, when applied, with the international research centers that cooperate in this study, in accordance with standard ethical procedures. In the case of ancillary studies, patients will be contacted to provide additional consent for the research team to use their data and biological specimens.

There will be no formal stopping rules, as this trial has minimum (if any) risk to the patients, given the characteristics of the intervention (very light physical activities). In addition, the follow up is relatively short, hampering any interim analysis that could precisely inform any eventual decision of interruption due to the lack of benefits or deleterious effects.

The researchers responsible for conducting the intervention and collecting the data along with at least two senior researchers will meet on a weekly basis, to discuss the progress of the protocol and eventual deviations from the original work plan. The ethics committee will be informed of any deviation. Upon study completion, the researchers will send a final report to the ethics committee, which will assess compliance to the ethics procedures.

### The Take a STAND for Health intervention

The Take a STAND for Health program is a newly developed, goal-setting, behavioral intervention aimed at reducing sedentary behavior (Fig. 3). Overall, this intervention consists of five face-to-face individual sessions, lasting approximately 15–30 min each. A trained researcher will conduct the individual sessions and patients will be instructed to choose goals to reduce sedentary behavior in the following domains: transport, work, and/or leisure and social activities. Patients will receive supportive phone calls and/or text messages on a weekly basis to check adherence to the goals. In addition, compliance will also be verified during individual meetings. More details on the interventions are presented in the next sub-sections. In a small pilot study in healthy young patients, we found that this program reduced sedentary time by 38 min/day after just 2 weeks (for further details see “Results and lessons from the pilot study”).

